#### Telephone assessment

A trained evaluator blinded to the study condition will administer all telephone interviews. As part of the interview, veterans will complete self-report measures: (1) the *PTSD Checklist-5* (PCL-5) [53] is a 20-item instrument that parallels criteria for a diagnosis of PTSD and (2) the attitudes and barriers toward seeking mental health services survey [54]. Finally, veterans will answer several questions regarding their reactions to the site. These items will appear at the end of the telephone interview to ensure that interviewers remain blind to the condition throughout the administration of the other interview components. All study participants will be reimbursed $30 upon completion of the telephone interview.

#### Qualitative assessment

Veterans in the *AboutFace * condition will answer a series of questions addressing reactions to this site. Sample questions will include the following: “Being as honest as possible, how much time did you spend on the site?”; “What questions on the site were you most interested in hearing the answers to?”; “Would you recommend this website to other Veterans?”; “What features did you like most about the site? What features did you like least?”; and “What suggestions do you have for improving the site?” Veterans in the usual care condition will be asked about general online health information seeking and use. Sample questions will include the following: “Do you use the Internet regularly?”; “Have you ever looked online for information about medical conditions?”; and “Have you ever looked online for information about emotional issues, such as anxiety, stress, mood, or other mental health issue?”

### Data analysis

#### Usability testing

A mixed method (qualitative/quantitative) analytic approach will be used for the pilot study. Qualitative data from interviews will be transcribed by a professional transcription service for later review. The qualitative approach chosen for this study is derived from constructivist-grounded theory, which acknowledges the researcher’s prior knowledge and influence in the qualitative analytic process and provides guidelines for building a conceptual framework to understand the interrelations (e.g., what and how) between constructs [55]. More specifically, grounded theory supports an *iterative* process in qualitative methodology that begins with “generative” questions that help guide the research but are not intended to be static or confining. Core concepts and themes are then identified by the researcher in an “ongoing” fashion during the data collection and coding process.

Codes will be generated through multiple close readings of the transcriptions by three (3) study members, who are trained and experienced in qualitative data analysis. Transcripts will be reviewed in batches of seven until a point of saturation is reached (i.e., point at which data collection will only confirm thematic categories and no additional data will be revealed). Based on individual readings, each author will independently create a list of thematic categories and subcategories. These themes will then be further developed and ordered by the primary reviewer ([name]). The authors will then meet as a group to discuss the categories, resolve questions, reduce redundancies in the data, and further refine the thematic categories. The study team has successfully used similar analytic approaches to qualitative research in their past work (e.g., [56–58]).

Triangulation is a method used by qualitative researchers to verify and minimize bias in their findings [59, 60]. We will use several triangulation methods to better interpret and verify the study data, including (a) data and methods triangulation (using different data collection measures and different sources of data—e.g., qualitative and quantitative measures and both self-report and interview data); (b) investigator and theory triangulation (having investigators with different backgrounds examine the data); and (c) collecting data until a point of saturation is reached.

With regard to data and method triangulation, a best-case scenario is that the results will prove to be mutually reinforcing. In the case of divergence, every effort will be made to look for patterns of inconsistencies and understand these differences in a manner that provides a more comprehensive understanding of the data. For example, it is anticipated that qualitative data regarding veterans’ reaction to *AboutFace * will converge with quantitative data that will be gathered from the Website Analysis and Measurement Inventory (WAMMI). However, investigators will explore areas of divergence across these data sources, should they arise, in order to better understand how to address barriers to care in the refinement of the intervention.

Generalized linear models (GLM) will be used to examine the associations of age, gender, race/ethnicity, urban/rural residence, and comorbidities with the WAMMI and questions around attitudes toward mental health treatment. We will examine the distribution of the measures to employ the appropriate link function for the model. GLM has been shown to be good for estimating models of mental health outcomes [61].

#### Feasibility testing

The feasibility trial will provide qualitative and descriptive data that we will use to assess the feasibility of our study methodology and to plan for a large-scale RCT. Experts strongly recommend that pilot grant mechanisms support evaluation of the feasibility and implementation of novel methods [62]. Researchers are cautioned to avoid testing hypotheses of efficacy or to attempt to calibrate effect sizes due to the inflated risk of type I or type II error with small samples [62–64]. Consistent with these guidelines, we are proposing to evaluate the feasibility of key assessment and implementation procedures that we plan to use in the larger RCT using a mixed method (i.e., qualitative/quantitative study) small-scale RCT.

For veterans randomized to both conditions, we will assess and describe several variables. Recruitment will be assessed by the proportion of patients who agree to participate as compared to the total number solicited to enroll. Study retention refers to the proportion of veterans enrolled in the study that complete the follow-up interview. This pilot will provide an opportunity to examine the feasibility of the study design and will yield pilot data such as (a) rate of recruitment into the study, including recruitment of rural, minority, and female veterans; (b) number and percentage of veterans in the *AboutFace* condition who use the site; (c) retention of veterans in the study protocol; (d) variability in data relating to stigma and attitudes toward seeking mental health services; (e) veterans’ reactions to the *AboutFace* site; and (f) preliminary data on treatment attendance across conditions.

We will estimate a logit model to examine the association of veteran age, gender, race/ethnicity, rural/urban residence, and comorbidities with the likelihood of dropping out of the study, measured as a binary variable, to understand where outreach efforts may need to be reinforced. The logit model will provide an odds ratio on each veteran factor along with a 95% confidence interval and *p* value. Logit models are often used to assess binary mental health outcome treatment outcomes [65]. We also will estimate a GLM to examine the association of veteran age, gender, race/ethnicity, rural/urban residence, and comorbidities with treatment attendance to assess the potential need for targeting vulnerable groups for improved attendance in treatment. The distribution of the attendance measure will be examined to choose the appropriate GLM link function for the model. All statistics will be performed in STATA 12 and significance based on *p* < 0.05. As this will be an underpowered study, we will provide 95% confidence intervals for all analysis estimates and all results will be treated with caution.

Coding and analysis of qualitative data will follow a similar procedure as that outlined above, with particular emphasis on data gathered from the experimental group regarding reactions to *AboutFace* (qualitative), attitudes toward seeking mental health services (quantitative), and sociodemographic variables. Again, these data sources will be used to better understand reactions to *AboutFace* and attitudes toward mental health treatment-seeking that can be used to refine the intervention for use across a diverse range of veterans. Similar to the usability component, convergence and divergence between data sources will be explored and reconciled to provide a more comprehensive picture of feasibility related to uptake and dissemination of *AboutFace*.

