### Participants and recruitment for usability testing

Usability testing will include individually-administered, in-person, semi-structured interviews with 20 veterans who are recommended for PTSD treatment following the completion of a diagnostic evaluation by PTSD clinical team (PCT) and Telehealth Program clinicians at the Ralph H. Johnson Veterans Affairs Medical Center (VAMC) in Charleston, SC. The use of semi-structured interviews for this stakeholder group was chosen for several reasons. First, *AboutFace* is highly relevant to veterans, who have recently attended a PTSD evaluation session. This approach will ensure that feedback is received from those who will be most likely to use and benefit from the site: veterans who are in the process of considering whether or not to seek mental healthcare. Second, this recruitment approach was chosen to ensure the feasibility of meeting sample recruitment goals and other milestones and study aims. Third, the sample of veterans recruited from this clinic will be heterogeneous, with about 30% who do not follow-up with treatment. Thus, the goal is to obtain feedback from veterans at different levels of treatment readiness.

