### Participants and recruitment for the feasibility trial

The recruitment and eligibility protocol for the feasibility trial will closely approximate that which will be used during usability testing. Eligible veterans will include those who are recommended for PTSD treatment following their completion of a PTSD evaluation conducted by the PCT. Recruited participants will include a racially and geographically-diverse sample of 60 veterans, including at least 20 veterans who are African-American, 20 veterans who are White, and of which at least 20 dwell in rural communities.

Study procedures will necessitate that eligible veterans have the ability to access the Internet. This can be done in the veteran’s household, in a VA facility, in a public library, or at the home of a friend or relative. We anticipate that this criterion will have minimal impact on eligibility. Evidence shows that 84% of adults in the USA use the Internet [25]. Roughly two-thirds of US adults access the Internet through mobile phone devices [50], and 44% of those who do not have their own accessible devices have gained access through family members [51]. These percentages are growing rapidly [52]. Therefore, the approach of the current study stands to reach the vast majority of veterans, through widely available technology.

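### The dropout logit puts five or more slopes on what is probably a handful of dropouts, so it may often have no finite estimate and is too imprecise to direct outreach

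*Protocol article*

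**What the plan says.** The feasibility trial's size is fixed under Participants and recruitment for the feasibility trial: "Recruited participants will include a racially and geographically-diverse sample of 60 veterans". The minima within that number are 20 African-American, 20 White and 20 rural veterans.

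The Feasibility testing section defines retention: "Study retention refers to the proportion of veterans enrolled in the study that complete the follow-up interview". It lists "retention of veterans in the study protocol" among the quantities that the pilot will yield. It then adds a regression: "We will estimate a logit model to examine the association of veteran age, gender, race/ethnicity, rural/urban residence, and comorbidities with the likelihood". The outcome is dropout, coded yes or no. Each factor gets an odds ratio, a 95% confidence interval and a p value. The purpose is "to understand where outreach efforts may need to be reinforced". The general rule follows: "All statistics will be performed in STATA 12 and significance based on" p < 0.05. The next sentence concedes that power is low, promises 95% intervals for every estimate and asks that results be read cautiously.

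The article gives no expected dropout rate, no coding for race/ethnicity or comorbidities, and no penalized or exact method.

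**The concern.** A logit is limited by the smaller of the two outcome groups, here almost certainly the dropouts. When there are few dropouts and several covariates, some covariate or combination of covariates can predict the outcome perfectly in the sample. Maximum likelihood then has no finite solution: at least one odds ratio runs to zero or infinity and its Wald interval and p value mean nothing. When the model does fit, the intervals may be too wide to separate a group that needs outreach from one that does not.

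The model has a practical job, which is to tell the team planning the larger trial where to reinforce outreach. If it fails or returns noise, the pilot loses usable information on which veterans drop out.

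**Working it through.** The article states no power or event figure for this model, so there is none to reproduce. The check has three parts.

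**Inputs from the article.** N = 60; five factors (age, gender, race/ethnicity, rural/urban residence, comorbidities); at least 20 rural veterans; significance at p < 0.05 (taken as two-sided).

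**Assumptions.** Dropout means not completing the follow-up interview. The rate is set at 10%, 15%, 20% or 30% of 60, which is 6, 9, 12 or 18 dropouts. The only nearby figure, under Participants and recruitment for usability testing, is "with about 30% who do not follow-up with treatment". It concerns treatment, not study dropout, and serves only as an upper scenario. Five slopes is the minimum (two race groups, one comorbidity term). Six applies if race/ethnicity has three levels, which the recruitment minima allow but do not require.

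**1. Dropouts per slope** = dropouts / slopes.

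| Dropout | Dropouts | Five slopes | Six slopes |
|---|---|---|---|
| 10% | 6 | 6/5 = 1.2 | 6/6 = 1.0 |
| 15% | 9 | 9/5 = 1.8 | 9/6 = 1.5 |
| 20% | 12 | 12/5 = 2.4 | 12/6 = 2.0 |
| 30% | 18 | 18/5 = 3.6 | 18/6 = 3.0 |

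The smaller outcome group cannot exceed 30 of 60, so no dropout rate gives more than 30/5 = 6 per slope.

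**2. Simulation of the planned logit.** There were 800-1000 trials per scenario: continuous age, 10-20% women, one-third rural, one comorbidity indicator at 50%, and race in two levels or in three (third group 10% or 33%). Separation, meaning no finite estimate for at least one coefficient, was detected by linear programming. The ranges cover the codings tried, with no true association.

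| Dropout | Separated, five slopes | Separated, six slopes |
|---|---|---|
| 10% | 45-64% | 54-84% |
| 15% | 23-43% | 30-67% |
| 20% | 11-29% | 15-52% |
| 30% | 2-19% | 2-31% |

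A repeat run under the same assumptions agreed to within simulation error.

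**3. What the model says when it fits.**
- The median ratio of upper to lower 95% limit for the rural odds ratio is about 43-50 at 10% dropout, 20-21 at 20% and 13-14 at 30%.
- Power to flag a true rural odds ratio of 3 (six slopes, 15% women, separated fits counted as not flagged) is 7%, 24% and 32% at 10%, 20% and 30% dropout. For an odds ratio of 2 it is 3%, 13% and 18%.
- With no true association, at least one factor reaches p < 0.05 in about 11-26% of fits that converge. For independent tests the figure would be 1 − 0.95^5 = 23% or 1 − 0.95^6 = 26%.

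**For comparison, the descriptive route** always gives a result. If 48 of 60 are retained (80%), the Wilson 95% interval is 68-88%. If 16 of 20 rural veterans are retained, it is 58-92%.

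**The case against.** **The numbers are not the plan's.** The article fixes neither the coding nor a dropout rate, so it does not commit to six slopes or to 6-12 dropouts, and the share of women in the simulation is also assumed. This stands, and is why the results are given as ranges. At 18 dropouts non-estimability is a minority outcome. Imprecision remains.

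**The plan already warns the reader.** A reader might infer that the p < 0.05 rule will turn a non-significant factor into a finding that no outreach is needed. The article does not say so, and its sentence on low power, intervals and caution points the other way. What the warning cannot do is supply an estimate where none exists, or narrow an interval.

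**Omission of randomized arm.** A reader might take this as a further cause of failure. The text does not support that. The stated aim concerns veteran characteristics, and an extra term does not relieve the sparsity: with arm as a seventh slope, separation is 77% at 10% dropout and 44% at 20%. Under Procedures for the feasibility trial, randomization follows entry of the access code on the portal, so enrolled veterans who never log in have no arm and could not enter such a model. Nothing in the article prevents retention from being reported by arm.

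**This is a detail for the analysis plan.** Coding and a sparse-data fallback could be left there. The method, covariates, outputs and purpose are fixed in the article, however, and it is that combination that fails.

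**One-factor models cannot disentangle correlated factors** such as race and rural residence. True, but 60 veterans cannot reliably do so in the full model either.

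**Conclusion.** The concern holds in a limited form. With at least five slopes and 60 veterans, the planned logit has about 1.0-2.4 dropouts per slope if 10-20% drop out, and 3.0-3.6 at 30%. Failure to produce a finite estimate is common at 6-9 dropouts, depends strongly on coding and rare categories at 12, and is less common at 18. Across all these scenarios the odds ratios are too imprecise to show where outreach is needed. These sizes rest on the assumed dropout rates, covariate mix and coding. The ceiling of 6 per slope rests on N = 60 and the five-slope minimum alone.

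The matter is of modest weight. The model is secondary and exploratory, overall retention is already planned as a simple proportion, and separation would be visible in the output. A change is worth making because it is cheap, not because the pilot's main results depend on it.

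**What to change.** - Make the main analysis retention by each veteran factor, with exact or Wilson 95% intervals and risk differences between groups.
- Where a model is wanted, use Firth-penalized logistic regression with one or two factors at a time, taking rural residence and race first because they carry recruitment targets.
- Judge outreach needs on estimates and intervals, and drop the p < 0.05 criterion for this aim.
- Describe retention by arm among randomized veterans, and report separately those enrolled who never log in and so have no arm. Arm need not enter the outreach models.

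The cost is analysis wording only; no data collection or sample size changes. What is lost is a set of mutually adjusted odds ratios for all factors, which 60 veterans cannot reliably supply. Subgroup intervals will still be wide, as the 58-92% example shows, but they will exist and will show their own uncertainty.

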## Discussion

PTSD is a prevalent, but undertreated, mental health problem among our nation’s veterans. Many veterans in need of mental health services are reluctant to seek care because PTSD is a stigmatized condition. Education may assist in addressing stigma, [66, 67] as well as knowledge, attitudes toward seeking mental health treatment, and service utilization [68–70]. Education that is delivered by peers who give first-hand accounts of their experiences may be particularly effective in accomplishing these goals. Uniquely, peer education delivered via DST is a low-cost, scalable, and sustainable aid to such efforts.

*AboutFace* is an ideal DST resource with which to initiate this line of research for several reasons. First, PTSD is a prevalent and stigmatized condition. Thus, a peer-to-peer approach may be particularly valuable for conditions where stigma may play a role in help seeking. Survey research has found that US adults with stigmatized illnesses (e.g., anxiety, depression, genital herpes, and urinary incontinence) were more likely than those with at least one other chronic illness (e.g., cancer, heart problems, diabetes, back pain) to have used the Internet for health information or to have communicated with providers via the Web [71]. Thus, what is learned during this research may have relevance to a wide range of stigmatized conditions. Second, *AboutFace* is a widely accessible resource that has already been developed and launched. Third, the clinician component of the resource is unique and will allow us to examine veterans’ use of, and reactions to, this educational content in addition to the peer education content. Data on veterans’ reactions may provide insight into the incremental value of expert content integrated into peer education resources.

### Future directions

Data obtained in this pilot will be used to guide planning in preparation for a large-scale RCT evaluation of AboutFace*.* More immediately, data will guide improvements to *AboutFace* that will be led by the National Center for PTSD. Usability testing data will inform an improved site design, such as changes to navigation, layout, and length of videos. Information on impact will guide next steps in the development process. In addition, the feasibility trial will allow for preliminary data on stigma, attitudes toward seeking help, and access to treatment. On each of these outcomes, we expect significant benefit ultimately at the population level. If not observed, additional videos could be added that more directly address these topics or, in some cases, new site features or components might be required. Upon completion of these improvements, the Center is prepared to immediately increase the marketing of the site through new social media avenues, as well as notices in the *PTSD Monthly Updates*. Resources directed to dissemination will be increased still further if data from the future planned RCT show clear benefits of *AboutFace* relative to stigma and access to treatment.

It is important to note that this study can serve as a model that can be implemented and have great potential with a wide range of treatment-seeking populations. This study’s methodology is easily translatable for researchers seeking to develop and/or improve other web/smartphone-based DST resources to improve relevance, interest, and effectiveness in decreasing stigma. Promisingly, this can be accomplished on both the disease (e.g., HIV, diabetes, obesity, and eating disorders) and demographic (e.g., veterans, civilians, and first responders) level. Technology-based DST resources hold great promise for engaging various treatment-seeking populations, and through the rigorous methodology found in this investigation, such resources have potential to reach these populations on an even greater level.

### Current status of the study

The study is registered on clinicaltrials.gov (Clinical Trial Identifier: NCT02486692). Usability testing was undertaken between August 2015 and January 2016. Participant recruitment for the feasibility trial began in March 2016 and is due to finish in September 2016.

## Abbreviations

CBOC: Community-based outpatient clinic
DST: Digital storytelling
GLM: Generalized linear modeling
OEF/OIF: Operation Enduring Freedom/Operation Iraqi Freedom
PCL-5: PTSD Checklist-5
PCT: PTSD clinical team
PTSD: Posttraumatic stress disorder
RCT: Randomized controlled trial
VA: Veterans affairs
VAMC: Veterans Affairs Medical Center
VHA: Veterans Health Administration
WAMMI: Website Analysis and Measurement Inventory
